## 1.9 RATIONALE

Patients with metastatic colorectal cancer are often treated with cetuximab +/- irinotecan in the 2nd or 3rd line setting. While some patients will have reasonably prolonged disease control, innovative strategies are still needed in previously-treated patients with metastatic colorectal cancer. We seek to determine the tolerability of combining a multi-targeted agent (ZD6474) with cetuximab and irinotecan in such a patient population and get preliminary data on the activity of such combinations.

## 2 OBJECTIVES

### 2.1 PRIMARY

The primary objective of this study will be to determine the tolerability and maximum tolerated dose (MTD) of combining ZD6474, cetuximab and irinotecan in patients with metastatic colorectal cancer refractory to prior cytotoxic chemotherapy.

### 2.2 SECONDARY

Determine response rate, progression-free survival and overall survival of adding ZD6474 to cetuximab and irinotecan in patients with metastatic colorectal cancer previously treated.

### 2.3 EXPLORATORY

We will explore whether molecular alterations within tumor blocks in VEGF, CD31 (for microvessel density), EGFR, p21, p53, p-AKT1, MSI, K-ras, and BRAF with responsiveness to therapy to seek for any tissue biomarker to predict responsiveness or resistance to the combination under study. We will explore changes in serum VEGF and other angiogenesis cytokine markers before and after initiation of ZD6474. See Appendix C.

## 3 STUDY SPECIFICATIONS

### 3.1 STUDY DESIGN

This is a Phase 1 trial in patients with previously treated stage IV colorectal cancer. The goal is to determine the maximum tolerated dose of ZD6474 with cetuximab and then the maximum tolerated dose of ZD6474, cetuximab and irinotecan.

During the dose finding phase, patients will be enrolled in cohorts of 3. All patients will receive standard doses of cetuximab (400 mg/m^2 loading followed by weekly 250 mg/m^2). Dose levels will be defined as such:

| Dose levels | ZD6474
(daily) | Irinotecan
(q2 wks) | Cetuximab †
(weekly) |
|-------------|-------------------|------------------------|-------------------------|
| 1           | 100 mg            | --                     | 250 mg/m    |
| 2           | 100 mg            | 180 mg/m   | 250 mg/m    |
| 3           | 200 mg            | 180 mg/m   | 250 mg/m    |
| 4           | 300 mg            | 180 mg/m   | 250 mg/m    |

† - after 400 mg/m^2 loading dose

The study will initially enroll into dose level 1. If 0 of 3 patients have a dose limiting toxicity (DLT) then we will advance to dose level 2. If 1 of 3 patients have a DLT, then 3 additional patients will be treated at dose level 1. If 2 patients have a DLT at

dose level 1, the study will close. If <33% of patients have a DLT at dose level 1, we will proceed to dose level 2.

At dose levels 2, we will initiate treatment with irinotecan. Treatment at dose levels 2-4 will begin with 2 weeks of only ZD6474 and Cetuximab. Irinotecan will begin on day 15 (week 3). If 0 of 3 patients have a DLT, we will proceed to the next dose level. If 1 of 3 patients have a DLT, then 3 additional patients will be treated at the same dose level. If 2 patients have a DLT, then the MTD will be current dose level -1 (if on dose level 1, study closes). If < 33% of patients have a DLT, then the study will continue to the next dose level (if at level 4, the MTD for ZD6474 will be considered 300 mg).

Cycles of therapy will be defined as 4 weeks on therapy, even if drugs are held for a portion of that time.

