## 5 STUDY PROCEDURES

### 5.1 TREATMENT REGIMEN

Treatment will be administered on an outpatient basis. Expected adverse events and appropriate dose modifications for study drugs are described in Section 6 and 7. No investigational or commercial agents or therapies other than those described below may be administered with the intent to treat the patient's malignancy.

This is a phase I study. Entry into dose levels are described in section 3. Initiation of ZD6474 will occur on the first day of treatment in the clinic or infusion unit. The patient will take the first dose of medication in the presence of the treating clinician or nurse. Thereafter, ZD6474 will be self-administered around the same time daily. If the patient inadvertently does not take the dose at their usual time, or has emesis within 30 minutes of taking ZD6474 tablet, the patient may take that dose any time

within 6 hours of the same day. The daily treatment schedule will be resumed the next day with the patient taking the scheduled dose at their usual time.

Cetuximab will be initiated on the first day of treatment at all dose levels. For the first treatment, ZD6474 should be given first and then at least 30 minutes should elapse prior to start of infusion of cetuximab. For the first treatment, patients will be premedicated with 50 mg IV of diphenhydramine 30-60 minutes prior to receiving 400mg/m^2 IV of Cetuximab over 120 minutes. Subsequently doses will be weekly infusions of 250 mg/m^2 IV over 60 minutes. The infusion rate of cetuximab must never exceed 10 mg/minute (5 mL/min). Premedication with diphenhydramine may be administered prior to subsequent doses, but at the Investigator's discretion, the dose of diphenhydramine (or similar agent) may be reduced.

In dose levels 2-4 and at the MTD (if includes irinotecan), irinotecan will be initiated on day 15 after administration of cetuximab. Irinotecan will be an IV infusion over 90 minutes every other week.

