### 13 Statistical Considerations

This is a phase I study, initially with dose escalation of ZD6474 and then adding irinotecan. The study will likely accrue between 6 and 15 patients (before MTD testing) with the described dose escalation schema, though it could range from 3 to 34 patients. We expect accrual to be 2-3 patients / month (though this will vary during waiting periods to proceed to next dose level). If patients in dose levels 2-4 who have a DLT in the first 14 days (prior to initiation of irinotecan), the patient will not be counted towards the DLTs of that cohort and an additional patient will be substituted. For example, if one of the first 3 patients in dose level 4 have a DLT, that patient will not be calculated into the DLT tabulation for ZD6474,

cetuximab and irinotecan and an additional patient will be substitute in that spot. If this scenario occurs twice, the study will be held and the study team will reevaluate the ZD6474 / cetuximab toxicity profile. To ensure the toxicity at the MTD is acceptable and to further define any toxicity that may occur with this regimen, an additional 10 patients will be accrued at the MTD. The estimation of toxicity rate will be based on these 10 additional patients. With 10 patients, the 90% confidence bounds for any toxicity will be  $\pm 28\%$ . The probability of a dose level declared too toxic based on the true DLT rate is defined as such:

| True DLT Rate | Probability of declaring dose too toxic |
|---------------|-----------------------------------------|
| 20%           | 0.29                                    |
| 30%           | 0.51                                    |
| 40%           | 0.69                                    |
| 50%           | 0.83                                    |
| 60%           | 0.92                                    |

Response rate, progression-free survival and overall survival are secondary analyses. Each will be reported by dose level and at the MTD.

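### If level 2 fails, Section 3.1 makes an irinotecan-free level the MTD of a three-drug combination, and its goal of a ZD6474-cetuximab MTD cannot be met under any outcome

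*Protocol*

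**What the plan says.** The primary objective in Section 2.1 is tolerability and the "maximum tolerated dose (MTD) of combining ZD6474, cetuximab and irinotecan". Section 7 names the same three-drug combination. Section 3.1 states a wider aim: "The goal is to determine the maximum tolerated dose of ZD6474 with cetuximab and then the maximum tolerated dose of ZD6474, cetuximab and irinotecan".

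The dose table in Section 3.1 has one level without irinotecan: level 1, ZD6474 100 mg with cetuximab. Levels 2, 3 and 4 give ZD6474 100, 200 and 300 mg, each with cetuximab and irinotecan 180 mg/m². At level 1, two DLTs close the study, and a DLT proportion below 33% leads to level 2. For levels 2-4 the stopping rule is "If 2 patients have a DLT, then the MTD will be current dose level -1 (if on dose level 1, study closes". If level 4 passes, "the MTD for ZD6474 will be considered 300 mg".

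Four other places bear on how the rule plays out:
- Section 3.2: at levels 2-4, a DLT in the first 14 days, before irinotecan starts, is not counted and the patient is replaced. If this happens twice, the study is held and the ZD6474-cetuximab toxicity is re-evaluated.
- Section 3.3: the expected number of patients depends partly on whether an MTD is tested.
- Section 5.1: irinotecan is started on day 15 at levels 2-4 and "at the MTD (if includes irinotecan".
- Section 13: ten more patients are accrued at the MTD, and the toxicity rate is estimated from those ten.

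**The concern.** The MTD is the primary result of this trial, so the rule that names it should return something that answers the objective. In one branch it does not: after a failed level 2 it points to a regimen with one drug fewer than the objective names. Section 13 then ties the ten-patient expansion and its toxicity estimate to that label. Sections 12.8 and 13 report efficacy at the MTD, while the secondary objective in Section 2.2 concerns adding ZD6474 to cetuximab and irinotecan.

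Separately, Section 3.1 announces an MTD for the doublet that the design has no means of finding. Section 13 also describes the sequence as "initially with dose escalation of ZD6474 and then adding irinotecan", and the opening phrase of the synopsis row on dose levels speaks of escalating irinotecan. The dose table does neither: irinotecan is added before ZD6474 is raised, and its dose is the same at every level that has it.

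**Working it through.** **Tracing the branches** (dose table and rules from Section 3.1; lead-in rule from Section 3.2)

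| Outcome | What the rule concludes | What the data would show |
|---|---|---|
| Level 1 fails | Study closes | 100 mg doublet exceeded the limit; no lower doublet level to fall back on |
| Level 1 passes | Go to level 2 | 100 mg doublet met the DLT rule; no higher doublet dose is put through it |
| Level 2 fails | MTD = level 1 | Lowest three-drug level exceeded the limit; no three-drug level met it |
| Level 3 or 4 fails | MTD = level below | A three-drug level exceeded the limit and the three-drug level below it met the rule |
| Level 4 passes | MTD of ZD6474 = 300 mg | All levels met the rule; none exceeded the limit |

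Levels 1 and 2 have the same ZD6474 dose and differ only in irinotecan. Stepping back from 2 to 1 therefore removes a drug; it does not lower a dose of the combination. Level 1 would not be a doublet MTD either, since no higher doublet dose was judged. The 14-day lead-ins at 200 and 300 mg do not fill that gap, because their DLTs are uncounted and two of them lead only to a hold.

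**Reproducing the protocol's table** (Section 13)

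A level passes on 0/3 or 1/6, since 2/6 = 33.3% is not below 33%. With true DLT rate p:

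P(pass) = (1−p)³ + 3p(1−p)² × (1−p)³, and P(too toxic) = 1 − P(pass).

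- p = 20%: 0.512 + 0.197 = 0.709, so P(too toxic) = 0.291 (stated 0.29).
- p = 30%: 0.343 + 0.151 = 0.494, so P(too toxic) = 0.506 (stated 0.51).
- At 40, 50 and 60% the formula gives 0.691, 0.828 and 0.918 (stated 0.69, 0.83, 0.92).

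The table is right for the rule. Applied to level 2, each figure is conditional on level 2 being reached.

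**Overall chance of the two branches**

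P(level 2 fails) = P(pass 1) × P(too toxic at 2). P(level 4 passes) is the product of the four pass probabilities. The protocol gives no expected DLT rates by level, so the profiles below are assumptions.

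| Assumed true DLT rates, levels 1-4 | Level 2 fails | Level 4 passes |
|---|---|---|
| 5/5/10/15% | 0.973 × 0.027 = 0.03 | 0.973 × 0.973 × 0.906 × 0.814 = 0.70 |
| 10/10/10/10% | 0.08 | 0.67 |
| 5/10/15/20% | 0.09 | 0.51 |
| 10/20/30/40% | 0.26 | 0.10 |
| 10/30/40/50% | 0.46 | 0.02 |
| 5/40/50/60% | 0.973 × 0.691 = 0.67 | 0.00 |

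Profiles that make one branch likely make the other unlikely.

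**How much a passed level says**

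A level with a true DLT rate of 10% passes with probability 0.91, and one at 30% with 0.49. The one-sided 95% upper bound on the DLT rate is 63% after 0/3 and 58% after 1/6. A pass means that the protocol's rule was met. It does not locate a maximum.

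**The case against.** The level 2 case was foreseen in part. Section 5.1 allows for an MTD without irinotecan, and Section 3.3 leaves open whether an MTD is tested at all. A reader might infer that ten more patients would certainly be treated on the doublet. Section 13 taken alone says so, but Section 3.3 prevents that conclusion; the sections are simply not reconciled. What stands is that foreseeing an irinotecan-free MTD does not make it the MTD of the combination in Section 2.1.

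The level 4 label is a convention declared in advance: the text says that the MTD is considered to be 300 mg. Section 1.7 also reports 300 mg as the MTD in earlier phase I studies of ZD6474. A reader might infer that the protocol claims an observed maximum. It does not, so this part is a matter of labelling. Passing level 4 would also still inform the tolerability half of the primary objective.

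The doublet MTD appears only in Section 3.1. The objectives and Section 7 do not ask for it, and the synopsis describes level 1 as a tolerability test, so no listed objective is lost. The loose descriptions of sequence in Section 13 and the synopsis are editorial, since the dose table and the sentences around it give the order clearly.

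Finally, the Alert Page shows level 4 effective from 03/26/2009, so in this trial the level 2 branch had already been passed.

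**Conclusion.** The point holds as a contradiction between the rule in Section 3.1 and the protocol's own objective, together with a stated goal that is unobtainable. Both follow from the text and need no numerical assumption. The level 4 label is a minor addition, though it is the part still live once level 4 has opened.

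The size of the level 2 problem is 0.29 to 0.51 once that level is reached, for true DLT rates of 20 to 30%. Overall it runs from about 0.03 to 0.67 under the assumed profiles, while the chance of passing level 4 runs from 0.70 to 0.00. A reader might put the 0.51 beside the 0.70 and infer that both wrong labels are likely in the same trial. They are not: the first is conditional on reaching level 2, and the second belongs to a profile in which level 2 fails about 3% of the time.

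Nor do the documents support reading this as a fault in the 3+3 rule or in its operating-characteristic table. The table reproduces, and the fault lies in what is concluded from the outcomes.

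**What to change.** State the conclusion by outcome in Section 3.1:
- If level 2 fails: no MTD of the three-drug combination was identified.
- If level 4 passes: MTD not reached; 300 mg is the highest dose level tested, and it met the protocol's DLT rule.

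Replace the goal of a ZD6474-cetuximab MTD with the tolerability of the level 1 doublet, as the synopsis already has it.

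Reconcile Sections 3.1, 3.3, 5.1 and 13 on whether and where the ten-patient expansion applies if level 2 fails. That decision belongs to the investigators, and this review does not propose it. Align the sequence described in Section 13 and the opening phrase of the synopsis row on dose levels with the dose table.

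The relabelling costs protocol wording only. It leaves the doses, the DLT definition, the escalation thresholds, the Section 13 table and the maximum enrolment (4 × 6 + 10 = 34) unchanged. The reported conclusions become slightly less favourable in the two branches concerned.

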### 3.2 DOSE LIMITING TOXICITIES

DLTs (defined as within the first 28 days of treatment in dose level 1 and first 35 days in dose levels 2-4) will include: grade IV hematological toxicity > 7 days; fever and neutropenia; grade III diarrhea leading to hospitalization or lasting > 48 hours despite aggressive anti-diarrheal medication; grade IV diarrhea despite aggressive anti-diarrheal medication; grade IV vomiting despite optimal antiemetics; or grade III or higher nonhematological toxicity (excluding nausea, vomiting, diarrhea, or alopecia) lasting > 1 week; grade 4 skin toxicity; grade 3 or greater cardiac toxicities; or death.

If patients in dose levels 2-4 who have a DLT in the first 14 days (prior to initiation of irinotecan), the patient will not be counted towards the DLTs of that cohort and an additional patient will be substituted. For example, if one of the first 3 patients in dose level 2 have a DLT, that patient will not be calculated into the DLT tabulation for ZD6474, cetuximab and irinotecan and an additional patient will be substitute in that spot. If this scenario occurs twice, the study will be held and the study team will reevaluate the ZD6474 / cetuximab toxicities.

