| Dose LEVELS                       | 
Phase I trial with sequential dose escalation of ZD7474 and irinotecan. We will initially test the tolerability of lowest dose of ZD6474 with standard dosing of cetuximab in dose level 1. If this combination is tolerable, then we will add standard dose every other week irinotecan and test for tolerability. We will then dose escalate ZD6474 with standard weekly cetuximab and every other week irinotecan.
 

Dose levels	ZD6474	Irinotecan	

1	100 mg	--	

2	100 mg	180 mg/m2	

3	200 mg	180 mg/m2	

4	300 mg	180 mg/m2	

                                                                                                                                                                                                                                                                                                                                                                                                                                                                                                                                                                                                                                                                                                                                                                                                                                                                                                                               | Dose levels | ZD6474 | Irinotecan | 1 | 100 mg | -- | 2 | 100 mg | 180 mg/m2 | 3 | 200 mg | 180 mg/m2 | 4 | 300 mg | 180 mg/m2 |

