**ALL PATIENTS WHO RECEIVE ONE DOSE OF TREATMENT SHOULD BE INCLUDED IN ANY SAFETY ANALYSIS.**

**THE INVESTIGATOR MAY DISCONTINUE THE TRIAL AT ANY TIME. REASONS FOR EARLY TRIAL DISCONTINUATION MAY INCLUDE, BUT ARE NOT LIMITED TO, UNACCEPTABLE TOXICITY OF STUDY TREATMENT, A REQUEST TO DISCONTINUE THE TRIAL FROM A REGULATORY AUTHORITY OR AN IRB, OR POOR ENROLLMENT.**

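### DLTs on days 1-14 at dose levels 2-4 are left out of the escalation tally, and the Section 13 probability table describes a rule that counts them

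*Protocol*

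**What the plan says.** Section 3.2 defines DLTs as events "within the first 28 days of treatment in dose level 1 and first 35 days in dose levels 2-4". It then adds that if a patient at levels 2-4 has a DLT in the first 14 days, "the patient will not be counted towards the DLTs of that cohort and an additional patient will be substituted". Two such events put the study on hold while the team reconsiders the ZD6474/cetuximab toxicities. Sections 7 and 13 repeat the rule, using levels 3 and 4 as their examples.

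Section 3.1 gives the surrounding design. "Treatment at dose levels 2-4 will begin with 2 weeks of only ZD6474 and Cetuximab", with irinotecan from day 15. No DLT in 3 patients escalates, 1 of 3 adds three patients, and "If 2 patients have a DLT, then the MTD will be current dose level -1". Passing level 4 makes 300 mg the ZD6474 MTD. The Synopsis (Dose Levels) says of the steps after level 2: "We will then dose escalate ZD6474 with standard weekly cetuximab and every other week irinotecan". Section 3.1 also states: "The goal is to determine the maximum tolerated dose of ZD6474 with cetuximab and then the maximum tolerated dose of ZD6474, cetuximab and irinotecan".

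Section 13 repeats the exclusion and, in the same paragraph, introduces a table with the words "The probability of a dose level declared too toxic based on the true DLT rate is defined as such". For true rates of 20, 30, 40, 50 and 60% it gives 0.29, 0.51, 0.69, 0.83 and 0.92.

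**The concern.** Days 1-14 are the first exposure to the only drug that changes between levels 2, 3 and 4. Leaving that period out of the tally is easy to follow at level 2, where irinotecan is the new element and the pair was already tested at 100 mg in level 1. At levels 3 and 4 the new element is the ZD6474 dose, and no cohort with fully counted DLTs has tested the pair at 200 or 300 mg.

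The primary endpoint is the MTD. A level could pass, and be expanded by 10 patients, with an early DLT that played no part in the decision. A reader relying on Section 13 would also misjudge how often the written rule passes a toxic level.

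**Working it through.** **Inputs.** The dose levels, the 14-day lead-in and the escalation rule come from Section 3.1. The DLT window, exclusion and hold come from Section 3.2, and the table from Section 13. The share f of 35-day DLTs that fall on days 1-14 is not given, so it is an assumption and is varied. An even hazard over the window would give f = 14/35 = 0.4.

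**Step 1: reproduce the table.** For a plain 3+3 with every DLT counted, P(too toxic) = 1 − [(1−p)³ + 3p(1−p)⁵]. This gives 0.291, 0.506, 0.691, 0.828 and 0.918 at p = 20 to 60%. All five match, so the table contains no exclusion, replacement or hold.

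**Step 2: the written rule, hold counted per level.** Each patient has an early DLT with probability e = fp (not counted, replaced), a counted DLT with probability l = (1−f)p, or none with probability n = 1−p. A level passes at 0/3 or 1/6 counted DLTs with at most one early DLT on the way:

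- P(pass) = n³(1+3e) + 3ln⁵(1+6e)
- P(too toxic) = l²[(1+2e) + 2n(1+3e) + 3n²(1+4e) + 3n³(1+5e) + 3n⁴(1+6e)]
- P(held) = the remainder

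At p = 0.4 and f = 0.4: e = 0.16, l = 0.24, n = 0.60.

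- P(pass) = 0.216 × 1.48 + 0.05599 × 1.96 = 0.320 + 0.110 = 0.429
- P(too toxic) = 0.391
- P(held) = 0.179

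**P(level passes), hold per level**

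| True 35-day rate | Implied by table | f=0.1 | f=0.25 | f=0.4 | f=0.5 |
|---|---|---|---|---|---|
| 30% | 0.494 | 0.535 | 0.585 | 0.623 | 0.641 |
| 40% | 0.309 | 0.346 | 0.393 | 0.429 | 0.448 |
| 50% | 0.172 | 0.199 | 0.233 | 0.262 | 0.277 |

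At f = 0 there is no difference.

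**Step 3: hold counted study-wide.** If one early DLT has already occurred at a lower level, the next one holds the study, so P(pass) = n³ + 3ln⁵. At p = 0.4 and f = 0.4 this is 0.216 + 0.056 = 0.272, below the table's 0.309.

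Over the whole escalation, simulation (100,000 runs per scenario, each hold treated as a stop) gave these probabilities that level 4 is declared the MTD. The DLT rates at levels 2/3/4 are assumed.

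| Assumed rates | Plain 3+3 | Hold per level, f=0.25/0.5/0.75 | Hold study-wide, f=0.25/0.5/0.75 |
|---|---|---|---|
| 15/25/45% | about 0.11 | 0.18/0.23/0.26 | 0.17/0.18/0.18 |
| 10/20/40% | about 0.20 | 0.29/0.35/0.38 | 0.26/0.29/0.28 |

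**Step 4: one cohort.** Patient 1 has a DLT on day 10, patient 2 on day 20, patient 3 none. If every DLT counts, this is 2 of 3 and the level is too toxic. Under Section 3.2 it is 1 of 2 with a place open. A counted DLT in the substitute makes the level too toxic; otherwise it is 1 of 3 and three more patients are added.

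**The case against.** The rule is deliberate. It appears in three sections with worked examples and serves the primary objective, the MTD of the three-drug combination. Section 3.2 qualifies Section 3.1 openly, so the two do not contradict each other on counting. If the table's true DLT rate means the rate among patients who are counted, the 3+3 formula is exact apart from the hold. That reading is coherent, but it is not the 35-day definition in Section 3.2, and Section 13 does not say it is meant.

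The size of f is open to challenge. Several DLT types must last more than a week, so they would have to begin by about day 7 to qualify by day 14. Irinotecan's main toxicities come after day 15. Both push f down. In the other direction, Section 6.3 places rash onset generally in the first three weeks, and Section 6.1 places 6 of 12 confirmed QTc prolongations in the first 28 days. These make f above zero plausible but do not fix it.

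A reader might infer three stronger points that the documents do not support:

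- **That the chance of stopping falls from 0.69 to 0.39** (true rate 40%, f = 0.4). A further 0.18 is held, and a hold also stops escalation. Like for like, stopping falls from 0.69 to 0.57.
- **That ZD6474 toxicity at 200 and 300 mg is ignored.** ZD6474 is taken daily, and DLTs on days 15-35 count.
- **That the early data are lost.** Section 11 says "ALL PATIENTS WHO RECEIVE ONE DOSE OF TREATMENT SHOULD BE INCLUDED IN ANY SAFETY ANALYSIS", the hold exists to review these events, and Section 13 adds 10 patients at the MTD.

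**Conclusion.** The point holds as a mismatch between the DLT definition, the counting rule and the stated operating characteristics. The table does not describe the written rule under the 35-day definition.

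With a per-level hold, the chance that a level passes exceeds the table's implied value at every early share above zero that was computed. At a true rate of 40% the excess runs from about 4 points (f = 0.1) to 14 points (f = 0.5).

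It would go too far to say that every level passes more easily. With a study-wide hold, a level entered after one early DLT can pass less often than the table implies. In the scenarios run, the chance of declaring level 4 the MTD still rose, by less than with a per-level hold.

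All sizes rest on an assumed f and on treating a hold as a stop. That the table is a plain 3+3, and that the scope and consequence of the hold are undefined, needs no assumption.

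**What to change.** Reconcile Sections 3.1, 3.2, 7 and 13 so that the DLT window, the counting rule and the table agree. Which counting rule applies is for the study team.

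- **If all DLTs from day 1 to day 35 enter the tally,** the table stands as printed.
- **If the exclusion stays:**
  - define the true DLT rate that the table uses;
  - recompute the table with three outcomes (too toxic, held, passes) over a stated range of f;
  - say whether the count of two early DLTs is per level or study-wide, and what a hold means for the MTD;
  - report DLTs before and after the start of irinotecan, by level;
  - check that the maximum of 34 allows for substitutes. It equals 4 × 6 + 10, which would leave no room for them, but that derivation is an inference.

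The cost is wording in Sections 3.2, 7 and 13, a short calculation and, if the exclusion stays, a less favourable table. The protocol's alert page shows accrual closed in May 2010, so the practical effect now is on how the MTD and the uncounted early DLTs are reported.
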